3.21 Inclusion criteria …………………………………………………………………………………………………………..4

3.21 Exclusion criteria ………………………………………………………………...………………………………………..4

1. **Study plan**4
   1. Phase of study4
   2. Sequence and timing5
   3. Protect privacy6
   4. Testing locations6
2. **Data analysis**7
   1. Statistical analysis7
   2. Subject confidentiality7
3. **Potential risks**7
   1. Risk from transcutaneous magnetic stimulation7
   2. Risk from interventions and experimental procedures8
4. **Potential benefits**8
   1. Subject benefit8
   2. Societal benefit8
5. **Investigator responsibilities**9
6. **Appendices**9
7. **References**9
8. **Background and Significance:**

Little progress has been made in developing any intervention that will enhance bladder function after a SCI. However our team has performed a systematic progression of experiments in animals and patients showing that several forms of electrical spinal cord stimulation can detect and improve spared function. We have implanted an epidural stimulation (EDS) electrode array over the lumbosacral spinal cord in 4 human subjects with a motor complete SCI. Each has gained some voluntary control of urinary voiding in the absence of EDS (1, 2). Furthermore, we have preliminary data showing that single-electrode TESS (transcutaneous electric spinal cord stimulation) and TMS (transcutaneous magnetic stimulation) of the cervical spinal cord can improve fine motor function of the upper limb in human subjects with incomplete quadriplegia. The critical question here is whether TESS or TMS can be used to enable spared function of sacral neuromotor networks, i.e., neural networks related to bladder function in animals and humans (3-6). The potential impact of these therapeutic interventions on the lives of individuals with urinary incontinence cannot be overestimated (7-9). Development of magnetic stimulation to activate spared, but silent, spinal cord pathways related to bladder function in humans could represent the beginning of a paradigm shift in the rehabilitative approach to bladder incontinence as a result of SCI and potentially other neurologic injuries or stroke (10-13). It could also provide new pathways toward more advanced technologies to further enable more potential success in improving bladder function.

As we have observed with studies of the lumbosacral spinal cord in completely paralyzed SCI subjects, future development of technical capabilities to use neuromodulation of the lumbosacral spinal cord for evaluation and enabling of spared function will undoubtedly enhance our ability to improve therapies for bladder function after paralysis. By discovering spared function and revealing the potential for treatments, the cost-savings from the proposed translational studies could include reduced assistive daily care costs, increased employment, and improved quality of life—especially for incomplete SCI patients who account for the majority of these SCI patients. The proposed studies could provide a partial solution to the US$40 billion/year care and $5.5 billion/year lost productivity costs (11, 14). Of the 10 million people in the US living with paralysis, 15,000 are the result of a SCI each year. The first year of care can range from $322,000-$986,000, with lifetime costs of $1.4-4M for someone injured at 25 years of age. In addition to potentially devastating sensorimotor disturbances, there is a huge financial cost of SCI, estimated to be $13.55B in medical care, therapy, and lost productivity nationwide. This proposal may positively impact patients with chronic or new SCI and other forms of nervous system damage or disease (stroke, multiple sclerosis).

1. ***Objectives***

The proposed study is to investigate the effectiveness of transcutaneous magnetic spinal cord stimulation can improve chronic spinal cord injured patients’ urinary function.

The pilot study is designed to enroll five subjects. It is designed with each subjects serving as their own control.

Hypothesis: transcutaneous magnetic stimulation can enable lumbosacral spinal circuitry to enable bladder control in chronic spinal cord injured individuals.

1. ***Subject Population***

3.1 Subject recruitment:

Recruitment of individuals with SCI will be from VA Greater Los Angeles, VA Long Beach, and UCLA Health Care System. Additional referrals will be generated from treating physiatrists, urologist, neurologists, and other clinicians at referral sites.

Initial contact will be made in person by a potential participant's physiatrist, urologist, neurologists or other clinician during an office visit. The potential participant will be provided with contact information, e.g. phone number, email address, of the PI, [name]. Once [name] has been contacted, he and his staff will schedule a visit by the potential subject for potential consent and enrollment.

3.2 Subject enrollment:

Prior to enrollment, the potential subject will be contacted by the PI. A phone questionnaire will be completed to ensure potential candidacy. The potential candidate will then be scheduled a visit to review the records and sign the informed consent in order to enroll.

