3.22 Exclusion criteria

- History of autonomic dysreflexia;
- Ventilator dependency;
- Musculoskeletal dysfunction, unhealed fracture, pressure ulcer, active infection;
- Clinically significant depression or ongoing drug abuse;
- Received botox injection, or bladder surgery (suprapubic access, Brindley procedure, etc.); prostatic hypertrophy or bladder outlet disorder;
- Cardiopulmonary disease that precludes lower extremity training or rehabilitation.

1. ***Study plan***
   1. *A description of each phase of the study. Details in Section 4.2.*

Phase # 1: Assessment—Define stimulation parameters that improve bladder function

Phase # 2: Treatment—Weekly stimulation to improve bladder function

Phase # 3: Follow-up—Determine the decay of stimulation effect

- 1. *Sequence and timing of study procedures to be performed.*

Phase # 1:

- - - - Urodynamic testing: Beginning and end
      - Bladder diary: Daily
      - Self assessment: SHIM, I-QOL: Beginning
      - Transcutaneous magnetic stimulation: weekly, 1Hz (low frequency) then 30Hz (high frequency)
      - ASIA Score: Beginning
      - Electrodiagnostic BCR: Beginning

Phase # 2:

- - - - Urodynamic testing: Start, monthly until conclusion (16 weeks)
      - Bladder diary: Daily
      - Self assessment: SHIM, I-QOL: end of phase
      - Transcutaneous magnetic stimulation: weekly with optimal stimulating parameter from Phase # 1
      - ASIA Score: End of the phase
      - Electrodiagnostic BCR: End of the phase

Phase # 3:

- - - - Urodynamic testing: Start (same as end of phase # 2)
      - Bladder diary: Daily
      - Self assessment: None
      - Transcutaneous magnetic stimulation: weekly sham
      - ASIA Score: End of phase
      - Electrodiagnostic BCR: none

**• Urodynamic testing** (a standard procedure for research purposes to determine bladder function):

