
1. ***Potential benefit***

7.1 Subject benefit: our hypothesis is that subjects will be able to have improved bladder control with transcutaneous magnetic stimulation. The subjects will therefore require fewer catherization and hence, lower likelihood of infection or traumatic injuries to the urinary tract. Furthermore, the subjects may experience improves sexual functions and bowel control.

7.2 Societal benefit: Importance of the Knowledge to Be Gained. The proposed experiments will demonstrate whether a new strategy of neuromodulation via non-invasive spinal cord stimulation can be used to improve bladder function. Positive demonstration of the proof-of-principle of the neuromodulatory strategy would almost certainly result in significant improvements in the quality of life after a spinal cord injury and could significantly reduce the cost of healthcare for these individuals by making them more independent. The knowledge gained also will demonstrate whether a medical stimulation device that is presently approved for other neuromotor dysfunctions can be used to improve bladder function. In addition we will learn whether a newly developed technology, transcutaneous stimulation, can be used to neuromodulate the spinal cord to improve bladder function. To date, there has been virtually no progress in improving bladder function after spinal cord injuries. The potential of the proposed studies are extremely positive. Given the magnitude of the scientific evidence from which the neuromodulatory strategy has evolved combined with our preliminary evidence in humans and rats, the potential gain that can be realized by so many impaired individuals given the modest total cost to be incurred in this grant cannot be denied.

1. ***Investigator responsibilities***

The principle investigator will be required to sign investigators agreement and adhere to the following:

- The protected health information requested is the minimum necessary to meet the research objectives
- The protected health information that is obtained as part of this study will not be used or disclosed to any other person other than study personnel except as required by law.
- Study Sponsors will not be provided with personal identifying information (including PHI) to take from the study site at any time, including the end of the study.
- Data and specimens shared with outside entities, such as study sponsors, will be coded or de-identified.

1. ***Appendices***

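### No bladder-diary period is scheduled before the first active stimulation, so the diary outcomes lack an untreated own-control baseline

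*Protocol*

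**What the plan says.** The Objectives section sets the size and the control: "The pilot study is designed to enroll five subjects", and "It is designed with each subjects serving as their own control". There is no comparison group.

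The steps before Phase 1 are in section 3.2 (Subject enrollment). After a telephone questionnaire, "The potential candidate will then be scheduled a visit to review the records and sign the informed consent in order to enroll". No diary is mentioned there.

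The schedule in section 4.2 then lists the diary in each of the three phases, always as "Bladder diary: Daily". In Phase 1 the same list gives "Transcutaneous magnetic stimulation: weekly, 1Hz (low frequency) then 30Hz (high frequency"; in Phase 2 it gives "Transcutaneous magnetic stimulation: weekly with optimal stimulating parameter from Phase # 1". Phase 3 replaces this with weekly sham.

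The description of the diary in section 4.2 says that it records voiding with and without a catheter, accidents and bladder infections, at 1–2 minutes per entry. Section 7.1 expects an improvement on one of these outcomes: "The subjects will therefore require fewer catherization".

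**The concern.** With five subjects and no control group, whatever is recorded before treatment is the only untreated reference. Section 4.1 describes the first phase as "Phase # 1: Assessment—Define stimulation parameters that improve bladder function", so it is a search for settings that work and not an untreated run-in. A diary that starts with that phase starts under treatment.

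The diary is the only listed record of how often subjects catheterise or leak in daily life. Urodynamics measure a supervised void in a supine subject, which is a different quantity. Entry requires intermittent catheterisation, but no pre-treatment frequency is scheduled. At stake is whether the expected reduction in catheterisations can be compared with each man's own untreated rate. An analysis plan cannot repair this, because it can choose among diary periods but cannot create one that was not collected.

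**Working it through.** The protocol gives no figure to reproduce on this point. The check sets the schedule entries side by side and then works through the possible contrasts.

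**Schedule (sections 3.2, 4.1 and 4.2)**

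| Period | Stimulation | Diary | Other measures |
|---|---|---|---|
| Enrolment | none | not listed | records review, consent |
| Phase 1 | active, weekly | daily | urodynamics, SHIM, I-QOL, ASIA, BCR at the beginning |
| Phase 2 | active, weekly | daily | urodynamics monthly; the others at the end |
| Phase 3 | sham, weekly | daily | urodynamics at the start, ASIA at the end |

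Diary periods scheduled before the first active session: 0. Diary periods under active stimulation: 2 (Phases 1 and 2). Diary periods without active stimulation: 1 (Phase 3), after all treatment.

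**Time available.** The study lasts 24 weeks. Reading the 16 weeks given for Phase 2 urodynamics as the length of that phase, 24 − 16 = 8 weeks remain for Phases 1 and 3 together. The split is not stated, and none of it is reserved for an untreated run-in.

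**Contrasts open to the diary data.** Let d be the true change in a diary outcome, full treatment minus untreated.

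1. *Phase 2 minus Phase 1.* If Phase 1 already produces f × d, the contrast is d − f × d = (1 − f) × d. The share lost is f. The protocol gives no f, so the values below are assumptions that show the range:
   - f = 0: 1 − 0 = 1, nothing is lost.
   - f = 0.25: 1 − 0.25 = 0.75, a quarter is lost.
   - f = 0.5: 1 − 0.5 = 0.5, half is lost.
   - f = 1: 1 − 1 = 0, the whole effect is hidden.
2. *Phase 2 minus Phase 3.* If a fraction r of the effect remains during sham, the contrast is d − r × d = (1 − r) × d, plus any change over calendar time, because Phase 3 always comes last. The protocol gives no r. Phase 3 exists to measure how the effect decays, so the plan itself allows for r above 0.
3. *Phase 2 minus an untreated run-in.* This estimates d without f or r, although change over time still enters. The current schedule does not provide it.

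Without pre-stimulation diary days, f cannot be estimated from the diary, so the reader of the results could not tell which of the cases under contrast 1 applies.

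**The case against.** The strongest reply is that the own-control design does not rest on the diary. Five other measures have an assessment at the beginning of Phase 1. Each urodynamic session also contains an own control, because the subject attempts to void for five minutes without intervention and then for five minutes with stimulation. Section 5.1 names electrophysiological and urodynamic data for analysis and does not name the diary. Section 7.1 describes potential benefit, puts improved bladder control first, and derives fewer catheterisations from it; it defines no endpoint. All of this stands. A reader might infer that the own-control design fails as a whole; the protocol does not support that.

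A second reply is that the bias is conditional. The first settings tried in Phase 1 may do little, in which case early Phase 1 is close to a baseline. If the effect decays fully, late Phase 3 is not attenuated by carry-over, though it remains confounded with time. This also stands. A reader might take a figure such as 25% to 50% understatement from the formula above, but that would only restate an assumed f of 0.25 to 0.5, for which the protocol gives no basis.

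Third, the diary is daily and stimulation weekly, and the day of the first session is not given, so some diary days could happen to fall before it. That is possible. The correct statement is that none is scheduled or defined as baseline, not that none can occur. Days that arise by chance may differ in number between subjects and could be absent in some of them.

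**Conclusion.** The point holds for the diary outcomes only: catheterisations, voids without a catheter, and accidents. For these the protocol schedules no period before the first active stimulation, and its only phase without active stimulation comes after treatment.

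The size of any bias cannot be fixed from the protocol. Phase 2 versus Phase 1 understates the effect by the fraction f that Phase 1 already delivers, from nothing at f = 0 upward. Phase 2 versus Phase 3 is biased toward no difference if the effect persists, and is confounded with time in any case. The reading of the schedule is firm; the direction of bias depends on these two conditions.

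Since the diary is not named as an endpoint or for analysis, this is an inexpensive improvement worth making and not a defect that undermines the study. It has to be made before a subject's first session, because a prospective baseline cannot be recovered afterwards.

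**What to change.** In section 4.2, start the daily diary at enrolment and require a defined run-in, for example 14 days, to be completed before the first active session. Name the run-in as the baseline for catheterisations per day, voids without a catheter per day and accidents per day. State that the last weeks of Phase 2 will be compared with it within subject. Phase 1 and Phase 3 diary data can still be shown to describe onset and decay.

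The cost is small. At 1–2 minutes a day, 14 days take 14 × 1 = 14 to 14 × 2 = 28 minutes per subject. The first session may move by up to about two calendar weeks, and the stated 24-week duration should be adjusted if needed. The 14 days are a suggestion and not a figure from the protocol; a different length works if it is fixed in advance. No sham sessions are needed in the run-in, and the stimulation schedule itself does not change.

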3.21 Inclusion criteria

- Male 18-75 years; This is required to have one urethral anatomy. Secondarily, more males have spinal cord injury, especially in veteran populations.
- At least 1 year post-injury;
- Non-progressive SCI at C2-T8 (non-conus injury);
- Motor Complete ISNCSCI ASIA Impairment Scale;
- Neurogenic bladder requiring clean intermittent straight catheterization;
- Able to attend weekly testing sessions for 6 months.
- Have intact lower extremity anatomy and able to use lower extremity for assistive standing and stepping. This is required to assess the quality of motor-function-activating spinal cord stimulation.

3.22 Exclusion criteria

- History of autonomic dysreflexia;
- Ventilator dependency;
- Musculoskeletal dysfunction, unhealed fracture, pressure ulcer, active infection;
- Clinically significant depression or ongoing drug abuse;
- Received botox injection, or bladder surgery (suprapubic access, Brindley procedure, etc.); prostatic hypertrophy or bladder outlet disorder;
- Cardiopulmonary disease that precludes lower extremity training or rehabilitation.

1. ***Study plan***
   1. *A description of each phase of the study. Details in Section 4.2.*

Phase # 1: Assessment—Define stimulation parameters that improve bladder function

Phase # 2: Treatment—Weekly stimulation to improve bladder function

Phase # 3: Follow-up—Determine the decay of stimulation effect

- 1. *Sequence and timing of study procedures to be performed.*

Phase # 1:

- - - - Urodynamic testing: Beginning and end
      - Bladder diary: Daily
      - Self assessment: SHIM, I-QOL: Beginning
      - Transcutaneous magnetic stimulation: weekly, 1Hz (low frequency) then 30Hz (high frequency)
      - ASIA Score: Beginning
      - Electrodiagnostic BCR: Beginning

Phase # 2:

- - - - Urodynamic testing: Start, monthly until conclusion (16 weeks)
      - Bladder diary: Daily
      - Self assessment: SHIM, I-QOL: end of phase
      - Transcutaneous magnetic stimulation: weekly with optimal stimulating parameter from Phase # 1
      - ASIA Score: End of the phase
      - Electrodiagnostic BCR: End of the phase

Phase # 3:

- - - - Urodynamic testing: Start (same as end of phase # 2)
      - Bladder diary: Daily
      - Self assessment: None
      - Transcutaneous magnetic stimulation: weekly sham
      - ASIA Score: End of phase
      - Electrodiagnostic BCR: none

**• Urodynamic testing** (a standard procedure for research purposes to determine bladder function):

Subject will be placed in supine position. Bladder will be emptied of existing urine by inserting a Foley catheter using aseptic technique and sterile equipment. Pre-warmed 37°C saline will be instilled at a rate of <30 mL/Min, to avoid any viscerosymapthetic reflex, until subject reports an urge to void, or 400 mL, whichever happens first. To avoid autonomic dysreflexia brought on by bladder filling (viscerosympathetic reflex), arterial blood pressure will be monitored and fluid infusion will be stopped after observing >10 mmHg increase in systolic and/or diastolic blood pressure and/or flushing. Intermittent ultrasound will be applied to assess any reflux and measure bladder distention. Rapid bladder emptying with Foley catheter will be performed if any of these changes was observed; if the symptoms do not improve nifedipine and nitrates (e.g., nitroglycerine paste or sublingual nitroglycerine) will be the next step of management. If there are any poor responses to treatment, the patient will be transferred to Ronald Reagan hospital for further management. Fluoroscopic imaging will be performed to avoid any vescicourethral reflux during the filling phase. Subject will then be asked to volitionally void without the use of any intervention for 5 minutes. Afterwards, the subject will be asked to void with the presence of transcutaneous or magnetic stimulation applied to the skin overlying the subject’s lower thoracic or lumbosacral spine for 5 minutes. Voided volume will be collected in a 1000 mL graduated plastic urinal. For the duration of the urodynamics testing, fluoroscopic imaging of the bladder and urethral sphincters will be performed intermittently, and rectal pressure, intravesicular pressure, external urethral sphincter and detrusor muscle pressures will be monitored and recorded. Upon completion of the test, the remaining saline instilled in the bladder will be emptied and recorded as residual volume. Duration: 60 minutes

**• Transcutaneous Magnetic Stimulation** (experimental procedure to attempt to activate *sacral parasympathetic nucleus (SPN) that contain parasympathetic preganglionic neurons* bladder-related circuits in the spinal cord): application stimulation coil to skin over the lower thoracic or lumbosacral cord spinal column (centered on midline lumbar-1 level). Application of 1-*30* Hz of stimulation. Stimulation amplitude will start at 1% Power (Magnetic stimulation) and will be increased in increments 1% Power (Magnetic stimulation) until the subject reports an urge to void or max tolerance. Maximum amplitude will not exceed 100% Power (Magnetic stimulation). Stimulation will be administered for 4 minute intervals at 3 times per session with 30 second break between intervals. Duration: 15-20 minutes

**• Self-Assessment** (standard procedures for research purposes): Incontinence Quality of Life (I-QOL), Sexual Health Inventory for Men (SHIM). Duration: 15 minutes

**• Bladder Diary** (standard procedure for research purposes): Subject will be asked to record voiding by catheterization or without catheterization. Number of accidents and bladder infections will be recorded, as well. Bladder diary will be performed at home. Duration 1-2 minutes

- 1. *How we will protect the privacy of the subjects during data collected.*

Patient will be consented in the clinic in a private room, behind closed doors. Subsequent testing will be conducted in a clinical research laboratory space in UCLA CTRC. All data collected will be placed on password protected files on an encoded hard drive. The data will be de-identified and coded key placed in a password protected file and on a separate encoded hard drive. The hard drives will be placed in a locked cabinet in the office of the PI in CHS, the door to the office is locked with only access from the PI, CHS is located behind security access points during off hours. Personally identifying information will be coded. Coding will be performed by a random number generator and code assigned to study participants. The coded key will be kept on a printout in a locked file cabinet behind a locked office door in CHS.

*• The approximate duration, intervals of administration and overall length of participation.*

1 hour for recruitment, 3 hours for enrollment. The study will take place over 24 weeks with weekly stimulation/testing and each session will take about 20 minutes – 1hr. 100 hours total.

- 1. *Testing locations:*

UCLA Clinical Translational Research Center (CTRC)

[name], Ambulatory Surgery Center

1. ***Data Analysis***

*5.1 Statistical analysis:*

All electrophysiological data from the TDT system (Tucker Davis Technologies, Alachua, FL) were exported to a personal computer and analyzed in MatLab (Matlab2015b, MathWorks, Natick, MA). The BCR amplitudes and latency were calculated for every single electrical pudendal stimulation. Spinal evoked potentials (if present) were identified in the continuous recording of lower extremity EMGs.

Urodynamic data were exported from the Laborie system to a personal computer and analyzed in Microsoft Excel (Excel2010, Microsoft, Redmond, WA). The changes in urethral pressure (P urethra) and detrussor pressure (P detrussor) were measured and compared during baseline and during attempted micturition.

Statistical significance was assessed with Analysis of Variance (ANOVA) and paired Student’s T-test using R 3.25 (https://www.r-project.org) and Graphpad Prism (Graphpad Software, La Jolla, CA), respectively.

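### Phase 3 is meant to measure decay of the stimulation effect, but urodynamics, I-QOL, SHIM and BCR have no value after it starts; only the bladder diary and ASIA score can show decay

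*Protocol*

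**What the plan says.** The list of phases in the protocol's Study plan (section 4.1) describes the last phase as "Phase # 3: Follow-up—Determine the decay of stimulation effect". No other purpose is given for it.

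The schedule in section 4.2 then sets out what is measured.

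- Phase 2: "Urodynamic testing: Start, monthly until conclusion (16 weeks"), with "Self assessment: SHIM, I-QOL: end of phase" and "Electrodiagnostic BCR: End of the phase". The diary is daily and the ASIA score is taken at the end of the phase.
- Phase 3: "Urodynamic testing: Start (same as end of phase # 2"), "Self assessment: None" and "Electrodiagnostic BCR: none". The diary stays daily, the ASIA score is taken at the end of the phase, and subjects have weekly sham stimulation.

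The diary covers voiding with and without a catheter, accidents and bladder infections. Section 5.1 names BCR amplitude and latency, and changes in urethral and detrusor pressure, as the data to be analysed.

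**The concern.** Decay is a change between two times: a value when active treatment ends and a later one. For four of the six measures in the schedule the plan has the first value and not the second. Each subject is his own control (section 2, Objectives), so no other arm can supply the missing contrast.

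The gap falls on the measures that the analysis section relies on. It also cannot be left to a statistical analysis plan, because no analysis can recover values that were never collected. Once a subject has finished Phase 3, the loss is permanent.

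**Working it through.** The protocol states no power, effect size or alpha for this aim, so there is no figure to reproduce. The check is a count of the assessments in section 4.2.

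**Step 1: values that bear on decay, per subject.**

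| Measure | At end of Phase 2 | New values after the start of Phase 3 |
|---|---|---|
| Urodynamics (pressures, voided and residual volume) | 1 | 0 |
| I-QOL | 1 | 0 |
| SHIM | 1 | 0 |
| BCR | 1 | 0 |
| ASIA score | 1 | 1 (end of phase) |
| Bladder diary | daily | daily |

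Over five subjects the first four rows give 5 × 0 = 0 post-treatment changes.

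**Step 2: identifiability.** Write the outcome at time t after the end of Phase 2 as level + slope × t. With the single time point t = 0 the design matrix is [1, 0], which has rank 1 for two parameters, so neither a slope nor a simple change can be estimated. One later time point raises the rank to 2. Runs with a second point at week 4 and at week 8 both gave rank 2.

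**Step 3: urodynamic sessions now in the plan.** The assumption is that monthly over 16 weeks means weeks 4, 8, 12 and 16; the protocol does not list the weeks.

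- Phase 1, beginning and end: 2
- Phase 2, start plus four monthly tests: 1 + 4 = 5
- Phase 3, new tests: 0
- Total: 2 + 5 + 0 = 7, or 6 if the end of Phase 1 and the start of Phase 2 are the same session

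Under either count, none falls after the start of Phase 3.

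**Step 4: what one added late value would give.** The five within-subject changes have 5 − 1 = 4 degrees of freedom. With two-sided alpha 0.05 (assumed, not in the protocol):

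- 95% CI half-width = t(0.975; 4) / √5 = 2.776 / 2.236 = 1.24 SD of the change
- mean change detectable with 80% power (paired t-test, noncentral t): about 1.68 SD

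Decay would become estimable, but imprecisely.

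**Step 5: length of Phase 3.** Section 4 gives 24 weeks in all. If Phase 2 takes 16 of them, Phases 1 and 3 share 24 − 16 = 8 weeks. The split is not stated, so the interval that a last-visit value would cover is unknown.

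**The case against.** The strongest reply is that Phase 3 does collect bladder data. The diary is daily and records catheterised and uncatheterised voids, and fewer catheterisations is the benefit to subjects named in section 7.1. A daily series describes the course of decay in more detail than one late urodynamic test could. This stands. A reader might infer that the trial can say nothing about decay, or nothing about voiding. The protocol does not support that. The diary does not, however, contain pressures, residual volume, quality of life or reflex data.

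A second reply is that the omissions are explicit entries and so look deliberate, and that the main objective concerns improvement, not decay. The main objective is indeed untouched: it rests on Phase 1 and Phase 2 data and on the unstimulated and stimulated voids within each urodynamic session. But a deliberate omission still leaves an aim that the schedule does not serve on these measures.

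Third, a reader might discount the diary as unblinded. The protocol does not say whether subjects know that Phase 3 is sham, so that cannot be asserted, and the point does not need it.

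Finally, the risk section (6.2) speaks of monthly video urodynamic testing. That remark is too general to add a Phase 3 test to an explicit phase-by-phase schedule.

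**Conclusion.** The point holds for urodynamics, I-QOL, SHIM and BCR: zero new values after the start of Phase 3 in all five subjects, so no estimate of decay or persistence on any of them. It does not extend to the diary or the ASIA score.

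It would also be wrong to infer that a late Phase 3 value would yield an active-versus-sham comparison. The order of the phases is fixed, so a change from the end of Phase 2 to the end of Phase 3 mixes loss of effect with sham exposure, time and order. One late value shows persistence at that visit, not the shape of the decay.

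The zero count rests only on the schedule as written. The total of 7 or 6 sessions rests on the reading of monthly in step 3, and the precision figures rest on the assumed alpha and on all five subjects completing. The mismatch should be settled before any subject reaches Phase 3.

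**What to change.** Amend the schedule in section 4.2 as follows.

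1. Give I-QOL and SHIM at the last Phase 3 visit. The cost is 15 minutes at a weekly visit that subjects already attend.
2. Place one urodynamic session at that visit without raising the total, so that the number of fluoroscopy exposures does not rise. If the end of Phase 1 and the start of Phase 2 are separate sessions, merge them and use the freed one; the cost is one fewer pre-treatment test. If they are already one session, nothing is freed, and one mid-Phase-2 monthly session has to move; the cost is one fewer on-treatment point. The protocol should say which case applies.
3. Report the per-subject change from the end of Phase 2 to the end of Phase 3 with a 95% CI. Label it a descriptive estimate of persistence, imprecise with five subjects and confounded with time and order, and not an active-versus-sham contrast.
4. Either repeat BCR at the same visit or state that BCR lies outside the decay aim.

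If the schedule is not changed, restrict the Phase 3 aim in section 4.1 to the bladder diary and the ASIA score. That needs only a change of wording, but it gives up any statement on persistence of the pressure and BCR results.
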